Appendix III(b).

**KESAN PEMBASMIAN JANGKITAN *HELICOBACTER PYLORI* DI KALANGAN PESAKIT PARKINSON**

Nama: _________________________________________

Nombor telefon: ____________________________________

Terima kasih kerana mangambil bahagian di dalam kajian ini.

Diari ini adalah untuk merekod status pergerakkan anda untuk 72 jam.

Diari ini hendaklah dilengkapi oleh anda. Penjaga anda boleh menolong mengisi ruang yang berkenaan. Sekiranya anda memerlukan bantuan, sila hubungi [name] ([name])

Sila tandakan satu kotak “status” sahaja bagi setiap waktu selang sejam dan pastikan tiada yang dibiarkan kosong.

Bagaimana untuk memilih kotak untuk ditanda:

1. Jika ubat memanfaatkan anda dari segi pergerakkan, perlahan dan kejang, sila tandakan kotak **“ON”** untuk selang waktu itu
2. Jika ubat memanfaatkan anda dari segi pergerakkan, perlahan dan kejang, tetapi anda mengalami pergerakkan memusing, memulas tanpa sengaja yang *tidak* menganggu fungsi atau *tidak* menyebabkan ketidakselesaan yang bermakna, sila tandakan kotak **“ON dengan diskinesia ringan”** untuk selang waktu itu
3. Jika ubat memanfaatkan anda dari segi pergerakkan, perlahan dan kejang, tetapi anda mengalami pergerakkan memusing, memulas tanpa sengaja yang menganggu fungsi atau menyebabkan ketidakselesaan yang bermakna, sila tandakan kotak **“ON dengan diskinesia bermasalah”** untuk selang waktu itu
4. Jika kesan ubat anda telah hilang dan tidak lagi memanfaatkan anda dari segi pergerakkan, perlahan dan kejang, sila tandakan kotak **“OFF”** untuk selang waktu itu.
5. Jika anda tertidur, sila tandakan kotak **“tertidur”** untuk selang waktu itu.
6. Dalam lajur terakhir, sila tandakan kotak yang sesuai dan nyatakan masa pengambilan **levodopa** anda.

NOTA: Diskinesia ialah pergerakkan memusing, memulas tanpa sengaja. Ini adalah kesan ubat dan berlaku semasa keadaan “ON”. Tremor ialah menggeletar dan TIDAK dianggap diskinesia. Hanya ANDA (pesakit) boleh memutuskan sama ada diskinesia tersebut bermasalah atau ringan.

| **HARI PERTAMA TARIKH:** | | | | | | |
| --- | --- | --- | --- | --- | --- | --- |
| **Masa** | **ON** | **ON dengan diskinesia ringan** | **ON dengan diskinesia bermasalah** | **OFF** | **Tertidur** | **Pengambilan Levodopa**  **(Nyatakan masa tepat)** |
| **0600-0700** |  |  |  |  |  |  |
| **0700-0800** |  |  |  |  |  |  |
| **0800-0900** |  |  |  |  |  |  |
| **0900-1000** |  |  |  |  |  |  |
| **1000-1100** |  |  |  |  |  |  |
| **1100-1200** |  |  |  |  |  |  |
| **1200-1300** |  |  |  |  |  |  |
| **1300-1400** |  |  |  |  |  |  |
| **1400-1500** |  |  |  |  |  |  |
| **1500-1600** |  |  |  |  |  |  |
| **1600-1700** |  |  |  |  |  |  |
| **1700-1800** |  |  |  |  |  |  |
| **1800-1900** |  |  |  |  |  |  |
| **1900-2000** |  |  |  |  |  |  |
| **2000-2100** |  |  |  |  |  |  |
| **2100-2200** |  |  |  |  |  |  |
| **2200-2300** |  |  |  |  |  |  |
| **2300-0000** |  |  |  |  |  |  |
| **0000-0100** |  |  |  |  |  |  |
| **0100-0200** |  |  |  |  |  |  |
| **0200-0300** |  |  |  |  |  |  |
| **0300-0400** |  |  |  |  |  |  |
| **0400-0500** |  |  |  |  |  |  |
| **0500-0600** |  |  |  |  |  |  |

| **HARI KEDUA TARIKH:** | | | | | | |
| --- | --- | --- | --- | --- | --- | --- |
| **Masa** | **ON** | **ON dengan diskinesia ringan** | **ON dengan diskinesia bermasalah** | **OFF** | **Tertidur** | **Pengambilan Levodopa**  **(Nyatakan masa tepat)** |
| **0600-0700** |  |  |  |  |  |  |
| **0700-0800** |  |  |  |  |  |  |
| **0800-0900** |  |  |  |  |  |  |
| **0900-1000** |  |  |  |  |  |  |
| **1000-1100** |  |  |  |  |  |  |
| **1100-1200** |  |  |  |  |  |  |
| **1200-1300** |  |  |  |  |  |  |
| **1300-1400** |  |  |  |  |  |  |
| **1400-1500** |  |  |  |  |  |  |
| **1500-1600** |  |  |  |  |  |  |
| **1600-1700** |  |  |  |  |  |  |
| **1700-1800** |  |  |  |  |  |  |
| **1800-1900** |  |  |  |  |  |  |
| **1900-2000** |  |  |  |  |  |  |
| **2000-2100** |  |  |  |  |  |  |
| **2100-2200** |  |  |  |  |  |  |
| **2200-2300** |  |  |  |  |  |  |
| **2300-0000** |  |  |  |  |  |  |
| **0000-0100** |  |  |  |  |  |  |
| **0100-0200** |  |  |  |  |  |  |
| **0200-0300** |  |  |  |  |  |  |
| **0300-0400** |  |  |  |  |  |  |
| **0400-0500** |  |  |  |  |  |  |
| **0500-0600** |  |  |  |  |  |  |

| **HARI KETIGA TARIKH:** | | | | | | |
| --- | --- | --- | --- | --- | --- | --- |
| **Masa** | **ON** | **ON dengan diskinesia ringan** | **ON dengan diskinesia bermasalah** | **OFF** | **Tertidur** | **Pengambilan Levodopa**  **(Nyatakan masa tepat)** |
| **0600-0700** |  |  |  |  |  |  |
| **0700-0800** |  |  |  |  |  |  |
| **0800-0900** |  |  |  |  |  |  |
| **0900-1000** |  |  |  |  |  |  |
| **1000-1100** |  |  |  |  |  |  |
| **1100-1200** |  |  |  |  |  |  |
| **1200-1300** |  |  |  |  |  |  |
| **1300-1400** |  |  |  |  |  |  |
| **1400-1500** |  |  |  |  |  |  |
| **1500-1600** |  |  |  |  |  |  |
| **1600-1700** |  |  |  |  |  |  |
| **1700-1800** |  |  |  |  |  |  |
| **1800-1900** |  |  |  |  |  |  |
| **1900-2000** |  |  |  |  |  |  |
| **2000-2100** |  |  |  |  |  |  |
| **2100-2200** |  |  |  |  |  |  |
| **2200-2300** |  |  |  |  |  |  |
| **2300-0000** |  |  |  |  |  |  |
| **0000-0100** |  |  |  |  |  |  |
| **0100-0200** |  |  |  |  |  |  |
| **0200-0300** |  |  |  |  |  |  |
| **0300-0400** |  |  |  |  |  |  |
| **0400-0500** |  |  |  |  |  |  |
| **0500-0600** |  |  |  |  |  |  |

Appendix III(c).

**KESAN PEMBASMIAN JANGKITAN *HELICOBACTER PYLORI* DI KALANGAN PESAKIT PARKINSON**

姓名: _________________________________________

电话号码: ____________________________________

谢谢您参与这次的研究。

这是一本记录您72小时运动机能的日记。

您需要亲自完成日记。您的护理员可以帮助您填写表格。

请在每半小时的间隔中只在日记页的一个“状态”空格内画勾并且确保完成了所有的一小时间隔。

**如何选择在什么空格里画勾**

1. 如果您的药物治疗对治疗灵动性，迟缓和僵硬有益，请在这半小时间隔的“**起效**”空格中画勾。
2. 如果您的药物治疗对治疗灵动性，迟缓和僵硬有益，但是您在体会不影响身体功能或不会引起重大的不适的偶然的扭曲，旋转运动，请在这半小时间隔的**“伴有轻微的（非棘手运动障碍）”**空格中画勾。
3. 如果您的药物治疗对治疗灵动性，迟缓和僵硬有益, 但是您在体会到影响身体功能或引起重大的不适的偶然的扭曲，旋转运动，请在这半小时间隔的**“伴有运动障碍”**空格中画勾。
4. 如果您的药物治疗效果减弱不再对治疗灵动性，迟缓和僵硬有益, 请在这半小时间隔的**“失效”**空格中画勾。
5. 如果您在熟睡中，请在这半小时间隔的**“熟睡”**空格中画勾。
6. 在最后的竖排中，请在合适的空格勾出您服用levodopa的时间。

注意：运动障碍是偶然的扭曲，旋转运动。这些运动不是药物的效用并且出现在起效时间内。颤动是来回地颤动并且不被认定为运动障碍。

只有您本人（患者）可以决定在任何的半小时时间中出现的运动障碍（偶然的扭曲，旋转运动）是棘手的还是轻微的（不棘手的）。

| **第 一 天 日期 ：** | | | | | | |
| --- | --- | --- | --- | --- | --- | --- |
| **时间** | **起效** | **非棘手**  **运动障碍** | **伴有**  **运动障碍** | **失效** | **熟睡** | **使用 Levodopa**  **写时间** |
| **0600-0700** |  |  |  |  |  |  |
| **0700-0800** |  |  |  |  |  |  |
| **0800-0900** |  |  |  |  |  |  |
| **0900-1000** |  |  |  |  |  |  |
| **1000-1100** |  |  |  |  |  |  |
| **1100-1200** |  |  |  |  |  |  |
| **1200-1300** |  |  |  |  |  |  |
| **1300-1400** |  |  |  |  |  |  |
| **1400-1500** |  |  |  |  |  |  |
| **1500-1600** |  |  |  |  |  |  |
| **1600-1700** |  |  |  |  |  |  |
| **1700-1800** |  |  |  |  |  |  |
| **1800-1900** |  |  |  |  |  |  |
| **1900-2000** |  |  |  |  |  |  |
| **2000-2100** |  |  |  |  |  |  |
| **2100-2200** |  |  |  |  |  |  |
| **2200-2300** |  |  |  |  |  |  |
| **2300-0000** |  |  |  |  |  |  |
| **0000-0100** |  |  |  |  |  |  |
| **0100-0200** |  |  |  |  |  |  |
| **0200-0300** |  |  |  |  |  |  |
| **0300-0400** |  |  |  |  |  |  |
| **0400-0500** |  |  |  |  |  |  |
| **0500-0600** |  |  |  |  |  |  |

| **第 二 天 日期 ：** | | | | | | |
| --- | --- | --- | --- | --- | --- | --- |
| **时间** | **起效** | **非棘手**  **运动障碍** | **伴有**  **运动障碍** | **失效** | **熟睡** | **使用 Levodopa**  **写时间** |
| **0600-0700** |  |  |  |  |  |  |
| **0700-0800** |  |  |  |  |  |  |
| **0800-0900** |  |  |  |  |  |  |
| **0900-1000** |  |  |  |  |  |  |
| **1000-1100** |  |  |  |  |  |  |
| **1100-1200** |  |  |  |  |  |  |
| **1200-1300** |  |  |  |  |  |  |
| **1300-1400** |  |  |  |  |  |  |
| **1400-1500** |  |  |  |  |  |  |
| **1500-1600** |  |  |  |  |  |  |
| **1600-1700** |  |  |  |  |  |  |
| **1700-1800** |  |  |  |  |  |  |
| **1800-1900** |  |  |  |  |  |  |
| **1900-2000** |  |  |  |  |  |  |
| **2000-2100** |  |  |  |  |  |  |
| **2100-2200** |  |  |  |  |  |  |
| **2200-2300** |  |  |  |  |  |  |
| **2300-0000** |  |  |  |  |  |  |
| **0000-0100** |  |  |  |  |  |  |
| **0100-0200** |  |  |  |  |  |  |
| **0200-0300** |  |  |  |  |  |  |
| **0300-0400** |  |  |  |  |  |  |
| **0400-0500** |  |  |  |  |  |  |
| **0500-0600** |  |  |  |  |  |  |

| **第 三 天 日期 ：** | | | | | | |
| --- | --- | --- | --- | --- | --- | --- |
| **时间** | **起效** | **非棘手**  **运动障碍** | **伴有**  **运动障碍** | **失效** | **熟睡** | **使用 Levodopa**  **写时间** |
| **0600-0700** |  |  |  |  |  |  |
| **0700-0800** |  |  |  |  |  |  |
| **0800-0900** |  |  |  |  |  |  |
| **0900-1000** |  |  |  |  |  |  |
| **1000-1100** |  |  |  |  |  |  |
| **1100-1200** |  |  |  |  |  |  |
| **1200-1300** |  |  |  |  |  |  |
| **1300-1400** |  |  |  |  |  |  |
| **1400-1500** |  |  |  |  |  |  |
| **1500-1600** |  |  |  |  |  |  |
| **1600-1700** |  |  |  |  |  |  |
| **1700-1800** |  |  |  |  |  |  |
| **1800-1900** |  |  |  |  |  |  |
| **1900-2000** |  |  |  |  |  |  |
| **2000-2100** |  |  |  |  |  |  |
| **2100-2200** |  |  |  |  |  |  |
| **2200-2300** |  |  |  |  |  |  |
| **2300-0000** |  |  |  |  |  |  |
| **0000-0100** |  |  |  |  |  |  |
| **0100-0200** |  |  |  |  |  |  |
| **0200-0300** |  |  |  |  |  |  |
| **0300-0400** |  |  |  |  |  |  |
| **0400-0500** |  |  |  |  |  |  |
| **0500-0600** |  |  |  |  |  |  |

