Appendix III. Motor Fluctuation Parkinson’s Disease Diary

**EFFECTS OF *HELICOBACTER PYLORI* ERADICATION IN PATIENTS WITH PARKINSON’S DISEASE.**

Name: _________________________________________

Contact No: ____________________________________

Thank you very much for participating in this study.

This is a diary to record your motor status for 72 hours.

The diary should be completed by you. Your caregiver can help in filling up the forms. In case you need any help with your diary completion, please contact [name] ([name])

Please tick only one “status” box for each hourly interval on the page and ensure that no hourly interval is left empty

How to select which box to tick:

1. If your medication was providing benefit with regard to mobility, slowness and stiffness, please tick **“ON”** box for that interval
2. If your medication was providing benefit with regard to mobility, slowness and stiffness, but you were experiencing involuntary twisting, turning movements that *did not* interfere with functioning or *did not* cause meaningful discomfort, please tick **“ON with minor (non-troublesome) dyskinesia”** box for that interval
3. If your medication was providing benefit with regard to mobility, slowness and stiffness, but you were experiencing involuntary twisting, turning movements that *interfered* with functioning or *caused* meaningful discomfort, please tick **“ON with troublesome dyskinesia”** box for that interval
4. If your medication had worn off and was no longer providing benefit with regard to mobility, slowness and stiffness, please tick **“OFF”** box for that interval
5. If you were asleep, please tick **“asleep”** box for that interval
6. In the last column, please tick the appropriate boxes and state the time you took your dose of **levodopa**

Note: Dyskinesias are involuntary twisting and turning movements. These movements are an effect of medication and occur during “ON” period. Tremor is shaking back and forth and is NOT considered dyskinesia. Only YOU (patient) can decide whether the dyskinesia is troublesome or minor.

| **DAY ONE DATE:** | | | | | | |
| --- | --- | --- | --- | --- | --- | --- |
| **Time** | **ON** | **ON with minor dyskinesia** | **ON with troublesome dyskinesia** | **OFF** | **Asleep** | **Levodopa Intake (state exact time)** |
| **0600-0700** |  |  |  |  |  |  |
| **0700-0800** |  |  |  |  |  |  |
| **0800-0900** |  |  |  |  |  |  |
| **0900-1000** |  |  |  |  |  |  |
| **1000-1100** |  |  |  |  |  |  |

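### The Chinese motor diary (Appendix III(c)) does not match the English and Malay diaries on what dyskinesia is or on how its columns are labelled, so its dyskinesia ticks may not mean the same thing

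*Protocol*

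**What the plan says.** The primary objective (Chapter 2, Study Objectives) concerns L-dopa onset time and on-time duration, both in minutes. Appendix III is a 72-hour diary in English, with a Malay version (III(b)) and a Chinese version (III(c)). Each hourly row offers ON, ON with minor dyskinesia, ON with troublesome dyskinesia, OFF and asleep, plus the time of levodopa intake.

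On the cause of dyskinesia:

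- English: "These movements are an effect of medication and occur during" the ON period.
- Malay: "Ini adalah kesan ubat dan berlaku semasa keadaan" ON, which has the same meaning.
- Chinese: "这些运动不是药物的效用并且出现在起效时间内". The movements are said not to be the drug's effect, and to appear during the ON time.

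On the third column:

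- English: "ON with troublesome dyskinesia".
- Malay: "ON dengan diskinesia bermasalah".
- Chinese: 伴有运动障碍, *with dyskinesia*, with no word for troublesome. This label stands in item 3 of the instructions and in the table header for all three days.

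The Chinese tick rules keep the split by function and discomfort. Item 2 covers movements that do not interfere ("但是您在体会不影响身体功能或不会引起重大的不适的偶然的扭曲，旋转运动") and item 3 covers movements that do ("但是您在体会到影响身体功能或引起重大的不适的偶然的扭曲，旋转运动"). The closing note leaves it to the patient to judge whether dyskinesia is troublesome or minor ("是棘手的还是轻微的（不棘手的").

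**The concern.** A translated diary is useful only if a tick in a given column means the same thing in each language. Here the Chinese form gives a different account of dyskinesia and a vaguer name for one of the two columns that record it.

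Of the forms shown, the diary is the only one that records ON and OFF interval by interval alongside levodopa times. The UPDRS form (Appendix VII) asks for the ON or OFF state at the examination, and in Part IV for dyskinesia and OFF time as broad bands of the waking day. It could not replace the diary.

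Three misreadings are possible:

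- A patient with minor dyskinesia could tick column 3 because its heading says only *with dyskinesia*.
- A patient with sustained dyskinesia could tick plain ON because the movements are described as occasional and not due to the drug.
- A patient who reads only the headings could fail to see columns 2 and 3 as ON states. Neither heading says ON, and 运动障碍 read literally is a movement impairment.

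**Working it through.** There is no sample size, power or error rate to reproduce. The check is a comparison of the three forms, followed by tracing what each kind of mistick would do to ON time.

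**Step 1. The three forms side by side**

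| Element | English (III) | Malay (III(b)) | Chinese (III(c)) |
| --- | --- | --- | --- |
| Cause of dyskinesia | Effect of medication | Effect of medication | Not the drug's effect (不是) |
| Word for involuntary | Involuntary | Unintended (tanpa sengaja) | 偶然的, occasional or accidental |
| Column 2 heading contains ON | Yes | Yes | No |
| Column 2 marked minor or non-troublesome | Yes | Yes | Yes (非棘手) |
| Column 3 heading contains ON | Yes | Yes | No |
| Column 3 marked troublesome | Yes | Yes | No |
| Tick rule split by function or discomfort | Yes | Yes | Yes |
| Interval named in the instructions | Hourly | Hourly | Half-hourly in most places, hourly once |
| Grid | Hourly | Hourly | Hourly |

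The cause sentence is reversed. The missing troublesome and the missing ON are omissions. The word 偶然的 is a mistranslation, and it recurs in items 2 and 3, in the note and in the closing sentence. It therefore sits inside the tick rules and not only in the explanatory text. The omissions are repeated in every day's table, so they are not a fault of text extraction.

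**Step 2. What a mistick would do to ON time**

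The protocol gives no scoring rule. Assume ON time = 60 × (c1 + c2 + c3) minutes, where c1, c2 and c3 count the ticks in the three ON columns.

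- *Minor dyskinesia ticked in column 3, k intervals.* c2 falls by k and c3 rises by k. Change in ON time = 60 × (−k + k) = 0.
- *Dyskinesia ticked as plain ON, k intervals.* c1 rises by k, and c2 or c3 falls by k. Change in ON time = 0.
- *A dyskinetic ON interval ticked as OFF, k intervals.* c2 or c3 falls by k and nothing replaces it. Change in ON time = −60k minutes over the 72 hours. For k = 1 that is −60 minutes, or 60 / 3 = 20 minutes per day.

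The first two shifts change only the dyskinesia split. Only the third reaches ON time. The figure for k = 1 shows the scale of a single tick and does not estimate how often the error occurs.

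**Step 3. How many diaries**

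The protocol does not state what share of patients will use each language, nor any rate of misreading. Neither the number of diaries affected nor the number of wrong ticks can be derived.

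**The case against.** The strongest reply is that the rules the patient follows are sound. Items 2 and 3 of the Chinese form turn on drug benefit plus interference or discomfort, as in the other languages. Column 2 is still headed non-troublesome, which tells the reader what column 3 must be, and the closing note repeats the choice. No rule asks the patient to attribute a movement to the drug, so the reversed sentence is background. The word 效用 may also mean a drug's intended benefit, which would soften the reversal. Finally, no dyskinesia outcome is named in the objectives, the hypotheses or the follow-up text of Section 4.5.

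Most of this stands, and it limits the consequence. A reader might infer that drug-induced dyskinesia is being misrecorded among users of the Chinese form. The document does not show that: it shows wording that could mislead someone who relies on the headings or the note. A reader might also infer that data from the three languages cannot be combined. That does not follow either. The comparison is before and after treatment in the same patients, and if each patient uses the same language form both times (an assumption), the wording is constant within the pair.

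The reply does not remove the errors. Even on the softer reading of 效用, the sentence does not say what the other two forms say. The term 偶然的 is inside the tick rules. And the headings, not the instructions, are what the patient sees when ticking each row.

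**Conclusion.** The point holds as a translation error to be corrected. Appendix III(c) differs from Appendices III and III(b) in the cause sentence, in the word for involuntary, in the label of column 3, and in the absence of ON from the headings of columns 2 and 3.

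Misclassification is a possible risk and its size is unknown. It bears mainly on the split between plain ON, minor dyskinesia and troublesome dyskinesia. If the three ON columns are summed, shifts among them leave ON time unchanged, and ON time moves only if a patient fails to recognise a dyskinesia column as an ON state. No effect on a stated endpoint is demonstrated.

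The correction is still worth making before use, because this form is completed by patients, it records ON and OFF by interval for a trial whose primary objective includes on-time duration, and the repair is nearly free. Confidence is high for the mismatch in the text and low for any effect on the results.

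**What to change.** Revise Appendix III(c) line by line against Appendix III:

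1. Change the note to say that dyskinesias are an effect of medication and occur during ON.
2. Replace 偶然的 with the term for involuntary (不自主) wherever it occurs.
3. Label column 2 as ON with minor (non-troublesome) dyskinesia and column 3 as ON with troublesome dyskinesia, in both the instructions and the header of each day's table.
4. In the same revision, reconcile the half-hour interval in the Chinese instructions with the hourly grid. The English and Malay forms are hourly throughout, and this mismatch bears more directly on recorded ON time than the dyskinesia labels do.

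Notify the ethics committee of the corrected form. If diaries have already been collected on the present form, record the language version for each patient and report the dyskinesia categories by version.

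The cost is the correction and reprinting of one translated form and one notification. No patients, visits or staff are added.

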Appendix IV (a)

**PDQ-39 Q**UESTIONNAIRE

|  | PATIENT ID |  | |  | |  | |  | |
| --- | --- | --- | --- | --- | --- | --- | --- | --- | --- |
| DATE OF ASSESSMENT |  |  | |  |  |  | |  |

**EFFECTS OF *HELICOBACTER PYLORI* ERADICATION IN PATIENTS WITH PARKINSON’S DISEASE**

**Please complete the following**

Please tick one box for each question

| No | Due to having Parkinson’s disease, how often during the last month have you…. | Never | Occasionally | Sometimes | Often | Always or cannot do at all |
| --- | --- | --- | --- | --- | --- | --- |
| 1 | Had difficulty doing the leisure activities which you would like to do? |  |  |  |  |  |
| 2 | Had difficulty looking after your home, e.g. DIY, housework, cooking? |  |  |  |  |  |
| 3 | Had difficulty carrying bags of shopping? |  |  |  |  |  |
| 4 | Had problems walking half a mile? |  |  |  |  |  |
| 5 | Had problems walking 100 yards? |  |  |  |  |  |
| 6 | Had problems getting around the house as easily as you would like? |  |  |  |  |  |
| 7 | Had difficulty getting around the public? |  |  |  |  |  |
| 8 | Needed someone else to accompany you when you went out? |  |  |  |  |  |
| 9 | Felt frightened or worried about falling over in public? |  |  |  |  |  |
| 10 | Been confined to the house more than you would like? |  |  |  |  |  |
| 11 | Had difficulty washing yourself? |  |  |  |  |  |
| 12 | Had difficulty dressing yourself? |  |  |  |  |  |
| 13 | Had problems doing up your shoe laces? |  |  |  |  |  |
| 14 | Had problems writing easily? |  |  |  |  |  |
| 15 | Had difficulty cutting up your food? |  |  |  |  |  |
| 16 | Had difficulty holding a drink without spilling it? |  |  |  |  |  |
| 17 | Felt depressed? |  |  |  |  |  |
| 18 | Felt isolated and lonely? |  |  |  |  |  |
| 19 | Felt weepy or tearful? |  |  |  |  |  |
| 20 | Felt angry or bitter? |  |  |  |  |  |
| 21 | Felt anxious? |  |  |  |  |  |
| 22 | Felt worried about your future? |  |  |  |  |  |
| 23 | Felt you had to conceal your Parkinson’s from people? |  |  |  |  |  |
| 24 | Avoided situations which involve eating or drinking in public? |  |  |  |  |  |
| 25 | Felt embarrassed in public due to having Parkinson’s disease? |  |  |  |  |  |
| 26 | Felt worried by other people’s reaction to you? |  |  |  |  |  |
| 27 | Had problems with your close personal relationships? |  |  |  |  |  |
| 28 | Lacked support in the ways you need from your spouse or partner?  *If you do not have a spouse or partner, tick here*  |  |  |  |  |  |
| 29 | Lacked support in the ways you need from your family or close friends? |  |  |  |  |  |
| 30 | Unexpectedly fallen asleep during the day? |  |  |  |  |  |
| 31 | Had problems with your concentration, e.g. when reading or watching TV? |  |  |  |  |  |
| 32 | Felt your memory was bad? |  |  |  |  |  |
| 33 | Had distressing dreams or hallucinations? |  |  |  |  |  |
| 34 | Had difficulty with your speech? |  |  |  |  |  |
| 35 | Felt unable to communicate with people properly? |  |  |  |  |  |
| 36 | Felt ignored by people? |  |  |  |  |  |
| 37 | Had painful muscle cramps or spasms? |  |  |  |  |  |
| 38 | Had aches and pains in your joints or body? |  |  |  |  |  |
| 39 | Felt unpleasantly hot or cold? |  |  |  |  |  |

Appendix IV (b)

**SOALAN KAJI SELIDIK PDQ-39**

|  | ID PESAKIT |  | |  | |  | |  | |
| --- | --- | --- | --- | --- | --- | --- | --- | --- | --- |
| TARIKH PENILAIAN |  |  | |  |  |  | |  |

**KESAN PEMBASMIAN JANGKITAN *HELICOBACTER PYLORI* DI KALANGAN PESAKIT PARKINSON**

**Sila lengkapkan soalan-soalan berikut**

Sila tandakan satu kotak untuk setiap soalan

| No. | Disebabkan oleh penyakit Parkinson, berapa kerap dalam tempoh sebulan yang lepas anda…. | Tidak pernah | Sekali-sekala | Kadang-kadang | Selalu | Sentiasa/ langsung tidak boleh buat |
| --- | --- | --- | --- | --- | --- | --- |
| 1 | Mengalami kesusahan membuat aktiviti lapang yang anda hendak lakukan? |  |  |  |  |  |
| 2 | Mengalami kesusahan mengurus rumah, sebagai contoh kerja rumah, memasak? |  |  |  |  |  |
| 3 | Mengalami kesusahan membawa beg ketika membeli-belah? |  |  |  |  |  |
| 4 | Mengalami masalah berjalan separuh batu? |  |  |  |  |  |
| 5 | Mengalami masalah berjalan 100 ela? |  |  |  |  |  |
| 6 | Mengalami masalah bergerak di sekitar rumah seperti yang anda kehendaki? |  |  |  |  |  |
| 7 | Mengalami masalah bergerak di khalayak ramai? |  |  |  |  |  |
| 8 | Menghendaki seseorang membantu anda keluar dari rumah? |  |  |  |  |  |
| 9 | Merasa takut atau risau akan terjatuh di khalayak ramai? |  |  |  |  |  |
| 10 | Berada di rumah lebih daripada apa yang anda jangkakan atau kehendaki? |  |  |  |  |  |
| 11 | Mengalami masalah membersihkan diri? |  |  |  |  |  |
| 12 | Mengalami masalah memakai baju sendiri? |  |  |  |  |  |
| 13 | Mengalami masalah memakai tali kasut? |  |  |  |  |  |
| 14 | Mengalami masalah menulis dengan senang? |  |  |  |  |  |
| 15 | Mengalami masalah memotong/memakan makanan sendiri? |  |  |  |  |  |
| 16 | Mengalami masalah memegang gelas tanpa tertumpah? |  |  |  |  |  |
| 17 | Merasa murung? |  |  |  |  |  |
| 18 | Merasa terpinggir dan keseorangan? |  |  |  |  |  |
| 19 | Merasa ingin menangis atau menangis? |  |  |  |  |  |
| 20 | Merasa marah atau geram? |  |  |  |  |  |
| 21 | Merasa cemas? |  |  |  |  |  |
| 22 | Merasa takut akan masa hadapan? |  |  |  |  |  |
| 23 | Merasa anda perlu merahsiakan penyakit Parkinson anda daripada diketahui orang? |  |  |  |  |  |
| 24 | Mengelakkan diri daripada suasana yang berkehendakkan makan atau minum di khalayak ramai? |  |  |  |  |  |
| 25 | Merasa malu di khalayak ramai kerana mengidap penyakit Parkinson? |  |  |  |  |  |
| 26 | Merasa bimbang mengenai reaksi orang terhadap anda? |  |  |  |  |  |
| 27 | Mengalami masalah mengenai perhubungan peribadi? |  |  |  |  |  |
| 28 | Kekurangan bantuan di mana anda kehendakinya daripada pasangan?  *Jika anda tidak mempunyai pasangan, sila tanda di sini*  |  |  |  |  |  |
| 29 | Kekurangan bantuan di mana anda kehendakinya daripada ahli keluarga atau kawan rapat? |  |  |  |  |  |
| 30 | Tidur pada waktu siang tanpa disangka? |  |  |  |  |  |
| 31 | Mengalami masalah memberi tumpuan, sebagai contoh ketika membaca atau menonton TV? |  |  |  |  |  |
| 32 | Merasa ingatan anda teruk? |  |  |  |  |  |
| 33 | Mengalami kesusahan khayalan atau halusinasi? |  |  |  |  |  |
| 34 | Mengalami masalah tentang percakapan? |  |  |  |  |  |
| 35 | Merasa susah untuk berkomunikasi dengan orang lain secara betul? |  |  |  |  |  |
| 36 | Merasa dipinggirkan oleh orang lain? |  |  |  |  |  |
| 37 | Mengalami kesakitan kejang otot atau kaku? |  |  |  |  |  |
| 38 | Mengalami sakit pada sendi atau badan? |  |  |  |  |  |
| 39 | Merasa tidak enak pada ketika panas atau sejuk ? |  |  |  |  |  |

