**KESAN PEMBASMIAN JANGKITAN *HELICOBACTER PYLORI* DI KALANGAN PESAKIT PARKINSON**

**柏金遜氏症生活質素問卷**

在過去的一個月，柏金遜氏症對你在下列各項的日常生活影有多少：

（每題請記擇最適合的一個答案；完成後請覆查每條問題是否已剔了一個答案）

|  |  | 從來沒有 | 偶然 | 有時候 | 經常 | 所有時候或  完全做不到 |
| --- | --- | --- | --- | --- | --- | --- |
|  |  | １ | ２ | ３ | ４ | ５ |
|  | 做從前喜歡的消遣活動時有困難 |  |  |  |  |  |
|  | 做家居工作（如煮飯，家務）時有困難 |  |  |  |  |  |
|  | 購物後攜帶所購物品時有困難 |  |  |  |  |  |
|  | 步行半哩（大約800米）時有困難 |  |  |  |  |  |
|  | 步行一百碼（大約90米）時有困難 |  |  |  |  |  |
|  | 在家中自由走動時有困難 |  |  |  |  |  |
|  | 在公眾場所內走動時有困難 |  |  |  |  |  |
|  | 外出時需要別人陪伴 |  |  |  |  |  |
|  | 在公眾場所內很或很擔心會跌倒 |  |  |  |  |  |
|  | 留在家中的時間比起自己希望的為長 |  |  |  |  |  |
|  | 替自己沐浴時有困難 |  |  |  |  |  |
|  | 替自己穿衣時有困難 |  |  |  |  |  |
|  | 替自己扣鈕或縛鞋帶時有困難 |  |  |  |  |  |
|  | 要清楚地書寫時有困難 |  |  |  |  |  |
|  | 用刀切食物時有困難 |  |  |  |  |  |
|  | 拿起水杯要保持不倒潟水會有困難 |  |  |  |  |  |
|  | 感到抑鬱 |  |  |  |  |  |
|  | 感到弧單和被隔離 |  |  |  |  |  |
|  | 感覺想哭或流淚 |  |  |  |  |  |
|  | 感到憤怒或苦澀 |  |  |  |  |  |
|  | 感到焦慮 |  |  |  |  |  |
|  | 替自己的將來感到憂慮 |  |  |  |  |  |
|  | 不想讓他人知道你有柏金遜氏症 |  |  |  |  |  |
|  | 盡量避免在公眾場合飲食 |  |  |  |  |  |
|  | 因自己患有柏金遜氏症，在公眾場合會感到尷尬 |  |  |  |  |  |
|  | 為別人對自己患病所作出的反應而感到擔心 |  |  |  |  |  |
|  | 親密的人際關係因患病而出現問題 |  |  |  |  |  |
|  | 缺乏配偶或伴侶所給予的支持  如沒有配偶或伴侶，請在空格內填 。 |  |  |  |  |  |
|  | 缺乏家庭或摯友所給予的支持 |  |  |  |  |  |
|  | 在日間無故地睡著 |  |  |  |  |  |
|  | 集中精神時有困難（如正有閱讀或觀看電視） |  |  |  |  |  |
|  | 覺得自己記憶力差 |  |  |  |  |  |
|  | 有發惡夢或出現幻覺的情況 |  |  |  |  |  |
|  | 說話時有困難 |  |  |  |  |  |
|  | 覺得自己不能與別人正常地溝通 |  |  |  |  |  |
|  | 覺得被別人忽視 |  |  |  |  |  |
|  | 肌肉有痛性抽筋 |  |  |  |  |  |
|  | 關節或身體部分覺得疼痛 |  |  |  |  |  |
|  | 對外界環境的冷或熱感到很不舒服  （例：進出空氣調節房間） |  |  |  |  |  |

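### The Malay PDQ-39 is not item-equivalent to the English and Chinese forms: item 37 adds stiffness and item 33 drops distressing dreams

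*Protocol*

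**What the plan says.** The Study Objectives name the PDQ-39, with UPDRS-III, as the measure for the secondary before-after comparison, and Chapter 3 repeats it in the second hypothesis. Section 4.5 gives a maximum total of 156 with eight subdivisions, and states that the instrument has been tested for reliability and validity. The forms are fixed in Appendix IV: (a) English, (b) Malay, (c) Chinese.

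- Item 37: English "Had painful muscle cramps or spasms"; Malay "Mengalami kesakitan kejang otot atau kaku". The Chinese item in the same position asks about painful muscle cramps only.
- Item 33: English "Had distressing dreams or hallucinations"; Malay "Mengalami kesusahan khayalan atau halusinasi"; Chinese "有發惡夢或出現幻覺的情況" (nightmares or hallucinations).
- Item 13: English "Had problems doing up your shoe laces", with the Malay form in agreement; Chinese "替自己扣鈕或縛鞋帶時有困難" (buttons or shoe laces).
- Item 15: English and Chinese ask about cutting food; the Malay form asks about cutting or eating it.

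The protocol does not give the share of patients on each form, and does not say that a patient uses the same form at both visits.

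**The concern.** A translated questionnaire can be pooled with its source only if each item asks the same thing. In Malay item 37, *kaku* (stiff) stands where the English has spasms. The Malay diary in Appendix III(b) also uses *kejang* for the stiffness that medication relieves: "Jika ubat memanfaatkan anda dari segi pergerakkan, perlahan dan kejang". A patient who has kept that diary therefore meets two stiffness words in one PDQ-39 item. In item 33, *khayalan* (imaginings) stands where the English has distressing dreams. Vocabulary was no obstacle, because the Malay non-motor questionnaire in Appendix V(b) uses *mimpi* for dreams.

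At stake is the meaning of the pooled PDQ-39 change. A patient's score on two items would depend partly on the language of the form, and the pooled result on the mix of forms. The validity testing cited in Section 4.5 does not automatically extend to a form whose item content differs. The forms are part of the protocol, and no analysis plan can recover a question that was never asked. The Malay form is unlikely to be marginal: under Section 4.1 an interpreter is provided only for people with a poor command of English or Malay.

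**Working it through.** **Step 1. Reproduce the stated maximum.** Section 4.5 lists subdivisions of 40, 24, 24, 16, 12, 16, 12 and 12.

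- Sum: 40 + 24 + 24 + 16 + 12 + 16 + 12 + 12 = 156, as stated.
- Items: 39 × 4 = 156, so each item carries 0 to 4 points.
- Dividing each subdivision by 4 and taking items in order puts items 30–33 in cognition (16) and 37–39 in bodily discomfort (12).

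**Step 2. Set the wordings side by side** (glosses are my own reading).

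| Item | English | Malay | Chinese |
| --- | --- | --- | --- |
| 37 | painful cramps or spasms | pain of muscle cramp, or stiff | painful cramps |
| 33 | distressing dreams or hallucinations | imaginings or hallucinations | nightmares or hallucinations |
| 13 | laces | laces | buttons or laces |
| 15 | cutting food | cutting or eating food | cutting food |

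On items 33 and 37 the Malay form stands alone in adding stiffness and in omitting dreams.

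**Step 3. Weight of the two main items.**

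- Total: 2 × 4 = 8 points; 8/156 = 5.1%.
- Item 37: 4/12 = 33% of bodily discomfort.
- Item 33: 4/16 = 25% of cognition.

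**Step 4. Effect of a one-category difference on item 37.** Take a patient whose stiffness changes by one category while cramps do not change, and who answers accordingly.

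- On the total: 1/156 = 0.64% of the range.
- On bodily discomfort: 1/12 = 8.3% of the range.
- The Malay-form share is not given. At an assumed 30% to 70%, the pooled total shifts by 0.64% × 0.3 = 0.19% to 0.64% × 0.7 = 0.45%. Pooled bodily discomfort shifts by 8.3% × 0.3 = 2.5% to 8.3% × 0.7 = 5.8%.
- These pooled figures assume that every Malay-form patient moves a full category, so they illustrate a high case.

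**Step 5. Direction.** Let *s* be the extra mean change in item 37 from adding stiffness, and *d* the mean change in the omitted dream content. A negative value means improvement. For a Malay-form patient, the difference in total change from an equivalent form is *s* − *d*. The protocol gives neither value, so I assume *s* from −1 to +0.5 and *d* from −1 to +1.

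- Lowest: −1 − (+1) = −2.0 points; −2.0/156 = −1.3% of the range, toward improvement.
- Highest: +0.5 − (−1) = +1.5 points; 1.5/156 = +1.0% of the range, toward worsening.
- Zero whenever *s* = *d*.

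The sign is not determined.

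**The case against.** A reader might infer more: that the Malay form gains a levodopa-responsive motor sign, loses a drug side effect, and so tilts the result toward benefit. The documents do not support this.

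- *Kesakitan* (pain) opens item 37 and most naturally governs the whole phrase. The item then asks about painful stiffness, not rigidity as a motor sign.
- Item 33 keeps hallucinations, which Table 1.1 marks as usually caused by medication. That table lists vivid dreaming under sleep dysfunction without such a mark. The UPDRS form in Appendix VII does grade vivid dreaming under a thought-disorder item attributed to dementia or drug intoxication, but it does not mention levodopa exposure. Side-effect content is narrowed, not lost.
- If dreams improve, omitting them hides a benefit.
- If stiffness improves because levodopa is better absorbed, that is the hypothesised effect, not an artefact. With the same form at both visits, the wording alters sensitivity but creates no false change by itself.
- Section 4.5 describes subscales, but the objectives and hypotheses name only the PDQ-39. Against the 156-point total the effect is small.

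These points stand, and they dispose of the directional claim. Two further defences carry less weight. The Malay form may have its own validation, which cannot be judged from the protocol; this is a reason to check its provenance and to allow a validated version as the remedy. Section 4.5 also has the investigator guide patients through the questionnaires, which might soften a loose wording, but it sets no rule for these items. None of this makes the items equivalent.

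**Conclusion.** The Malay PDQ-39 departs in content from the English and Chinese forms on items 33 and 37, with smaller departures in items 13 (Chinese) and 15 (Malay). The pooled change therefore mixes slightly different measures. Items 33 and 37 bear on 5.1% of the total score, but on a quarter of cognition and a third of bodily discomfort, so the point matters most if subscales are reported. This is a modest defect in a secondary outcome; it does not touch the levodopa onset and on-time endpoints or the sample size. A bias toward improvement is not shown, since on the assumed changes the effect can take either sign.

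The conclusion rests on my reading of the Malay and Chinese, which a qualified translator should confirm. The sizes in steps 4 and 5 also rest on an assumed form share and assumed item changes.

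**What to change.** Before use, have a qualified translator reconcile the Malay and Chinese items with the English source. Item 33 should include distressing dreams, item 37 should ask about painful cramps or spasms, and items 13 and 15 should match across forms. Alternatively, substitute an existing validated translation. State in Section 4.5 that each patient completes the same language form at baseline and at three months.

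If the forms are already in use, keep them for patients who have started, record which form each patient used, and report the PDQ-39 change with and without the non-equivalent items as a sensitivity analysis.

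The cost is a reprint with a translator's check, or one extra analysis. No additional patients or visits are needed.
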